# PATIENT REPORTED OUTCOMES (PROMS)

When evaluating quality of life among women with endometriosis many different scales have been used, mostly of generic character that are not specific to the disease. One of these is 30-item Endometriosis Health Profile (EHP30), a scale that perform well in clinical practice in the routine evaluation of Health-Related Quality of life (HRQoL) The use of EHP30 is recommended by the National Board and Welfare in Sweden, the ASRM and ESHRE (40). Using EHP-30, a small study has shown an improvement in HRQoL in the follow-up after endometriosis surgery, an effect that may last for up to 6.8 years (41). Two recent studies show postoperative improvement in HQQoL measured by EHP-30 10 weeks and 3 months after surgery, respectively (42, 43). Especially women with deep endometriosis (DE) showed a more significant benefit from surgery (43). However, HRQoL can also be affected by infertility, and in this trial, infertility treatment will be delayed, thus, HRQoL is an important measurement.

POINTS OF ASSESSMENT

Baseline assessment will be obtained after randomization and maximum 1 month prior to surgery or start of first ART cycle

Thereafter assessment will be done prospectively at:

- 2 months after surgery (for the group randomized to first line surgery)
- 1:st oocyte pick up (for both randomization groups)
- 2 months after 1:st oocyte pick up
- 2:nd oocyte pick up
- 2 months after 2:nd oocyte pick up
- 3:rd oocyte pick up
- 2 months after 3:rd oocyte pick up
- Visit, phone call or questionnaire 3 years after randomization.

Compliance with completing the questionnaires will be investigated at each time point to

evaluate the procedure for data collection and the feasibility of the questionnaires.

INSTRUMENTS

The core questionnaire in EHP -30 includes 30 questions in 5 health-related areas: pain, control and powerlessness, emotional well-being, social support, and self-image. In addition, there are six supplementary modules covering work, relationship with child/children, sexual relationship, feelings about the medical profession, feelings about treatment and feelings about infertility.

The Numeric Rating Scale (NRS) is a frequently utilized pain assessment tool commonly employed in postoperative care. It allows for the momentary evaluation of pain on a scale from 0 to 10, with 0 representing "no pain" and 10 indicating "the worst pain imaginable”.

EQ-5D is a standardized non-disease specific instrument for describing and

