# HEALTH ECONOMICS

Health economics will be analyzed with respect to Swedish conditions first and with an international perspective.

DIRECT COSTS

To evaluate healthcare costs, the internal accounting and billing systems within hospitals will be utilized to estimate direct costs based on Cost Per Patient (CPP) principles for individual treatments and/or Diagnosis-Related Groups (DRG) for surgery and fertility treatment. We will also obtain CPP and/or DRG-based cost data from the hospitals where the included women receive care in connection with surgery, fertility treatments, pregnancy, childbirth, and postpartum follow-up. In addition, data on employment status at baseline will be collected. Quality-Adjusted Life Years (QALY) will be computed using data from the EQ-5D instrument. Variations in changes to health status and quality of life will be utilized for a cost-utility analysis, with the results presented as an Incremental Cost-Effectiveness Ratio (ICER). This analysis will provide insights into the additional cost per year of full health achieved with first line surgery compared to first line ART.

INDIRECT COSTS

To assess indirect costs related to the disease, both study arms will be examined with regard to estimating productivity costs, specifically the level of decline in production. Methods such as the friction cost method may be employed for this purpose.

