**Quality of Life and Health Status Measures:**

**EHP-30 (continuous, 0–100 scale):**
Analyzed using a linear mixed-effects model (LMM) with random intercepts for participants. Fixed effects will include treatment group, time, and the treatment×time interaction, adjusting for prespecified covariates (age, BMI, AMH, center).

**EQ-5D (continuous index 0–1):**Analyzed using the same LMM framework as EHP-30 (random intercepts, treatment, time, treatment×time, prespecified covariates).

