**NRS pain (ordinal: mild 1–3, moderate 4–6, severe 7–10):**
Analyzed using a generalized linear mixed model (GLMM) with cumulative logit link (ordinal logistic regression), including random intercepts for participants, fixed effects for treatment, time, and treatment×time, and prespecified covariates (age, BMI, AMH, center).

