**Health economics**
A cost-effectiveness analysis will be conducted from the healthcare perspective. Incremental cost-effectiveness ratios (ICER) will be calculated based on QALYs, and probabilistic sensitivity analyses will be performed to address parameter uncertainty.

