**Additional analysis**

– Exploratory subgroup analyses will not be adjusted for multiplicity.

– Safety outcomes will be summarized descriptively by treatment group (frequency, severity, relation to treatment).
– All available data will be used, including outliers.
– Missing outcome data will be handled under the missing-at-random assumption via maximum likelihood in mixed models; for regression models requiring complete covariates, complete-case analysis will be applied.

Covariates

Primary and secondary outcomes will be adjusted for prespecified covariates (age, BMI, AMH, ART type, center), chosen based on clinical relevance and prior evidence.

POWER CALCULATION AND SAMPLE SIZE

The sample size calculation was based on a two-sample comparison of proportions with a two-sided α=0.05 and 80% power. Based on observational data (18, 19), the cumulative live birth rate (CLBR) after three IVF cycles was assumed to be 55% in the ART-only group and 71% in the surgery+ART group (relative risk ≈1.29). This yields a required sample size of 142 participants per arm (284 total). Allowing for 20% attrition, the planned total sample size is 350 participants.

The necessary sample size for this study is estimated to 323 patients to accommodate a statistical analysis method. This estimation uses the 'pwr' package in R, specifically employing the power.prop.test method, which is designed to compare two proportions. This method is more aligned with contemporary statistical practices and provides a clear, transparent methodology for determining the required sample size based on expected success rates.

This means inclusion of 29 patients from/each center/year and 15 surgeries/year. In a Swedish study published in 2022 the prevalence of endometriosis in patients referred for ART-treatment was 21.8% and 17.2% of women had DE (14). In 2021 almost 10 500 IVF cycles were performed in Sweden, while more than 5 500 of those were first-time IVF/ICSI with autologous gametes ((46) Figure 22).

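### The EHP-30, EQ-5D and NRS pain models omit the baseline value of the score, which the trial already collects, so their arm comparisons are less precise than they could be

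*Protocol*

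**What the plan says.** Under Quality of Life and Health Status Measures in Statistical Considerations, the EHP-30 model is a linear mixed model with a random intercept per woman. Its terms are: "Fixed effects will include treatment group, time, and the treatment×time interaction, adjusting for prespecified covariates (age, BMI, AMH, center"). For EQ-5D the protocol says: "Analyzed using the same LMM framework as EHP-30 (random intercepts, treatment, time, treatment×time, prespecified covariates"). NRS pain, in three ordered categories, has a cumulative-logit mixed model with "fixed effects for treatment, time, and treatment×time, and prespecified covariates (age, BMI, AMH, center").

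The Covariates paragraph later in the same chapter is slightly wider: "Primary and secondary outcomes will be adjusted for prespecified covariates (age, BMI, AMH, ART type, center"). It adds ART type. The baseline score is in none of these lists.

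The baseline score is collected. The chapter on patient reported outcomes states: "Baseline assessment will be obtained after randomization and maximum 1 month prior to surgery or start of first ART cycle". The Schedule of Events places this assessment in the same row as the follow-up questionnaires. The Procedure paragraph adds that the first questionnaire kit is handed out once the woman has been told her arm, and the trial is open label.

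**The concern.** The earlier value of a patient-reported score is normally the strongest single predictor of its later value. A covariate list that names age, BMI, AMH and center but not that value leaves explainable variation in the residual. Whether surgery gives better quality of life and less pain is a stated secondary objective. The intervals on those comparisons would be wider than the collected data require.

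The text also leaves the contrast itself undefined. If time includes the baseline visit, treatment×time measures change from baseline. If time starts after baseline, it measures a plain follow-up difference. The two react in opposite directions to a baseline difference between arms, and neither is the efficient choice.

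**Working it through.** **The protocol's own figure.** The only design calculation is for live birth, 55% against 71%, two-sided α = 0.05, 80% power. With the pooled-variance formula, n = [1.96·√(2·0.63·0.37) + 0.842·√(0.55·0.45 + 0.71·0.29)]² / 0.16² = 141.8, so 142 per arm, as stated. No correlation, SD or power is given for EHP-30, EQ-5D or NRS, so 142 per arm serves below only as an illustrative size.

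**Inputs.** Let ρ be the correlation between baseline and follow-up score, with equal variances at the two times. It is assumed at 0.3, 0.5 and 0.7.

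**Variance of the arm contrast at one visit, in units of 2·SD²/n:**
- raw follow-up difference: 1
- change from baseline: 2(1 − ρ)
- baseline as covariate: 1 − ρ²

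Since 1 − ρ² = (1 − ρ)(1 + ρ), the adjusted variance is (1 + ρ)/2 of the change variance. It is therefore below both alternatives whenever 0 < ρ < 1.

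| ρ | Raw | Change | Adjusted | Cut against change | Cut against raw |
|---|---|---|---|---|---|
| 0.3 | 1 | 1.40 | 0.91 | 35% | 9% |
| 0.5 | 1 | 1.00 | 0.75 | 25% | 25% |
| 0.7 | 1 | 0.60 | 0.51 | 15% | 49% |

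**Detectable difference, 80% power, illustrative 142 per arm.** The raw value is (1.96 + 0.842)·√(2/142) = 0.332 SD; the others follow by multiplying by the square root of the variance above.
- change: 0.393, 0.332, 0.258 SD
- adjusted: 0.317, 0.288, 0.237 SD

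**Power.** For a contrast that would otherwise have 80% power, power after adjustment is Φ(2.802/√ratio − 1.96).
- against the change contrast (ratios 0.65, 0.75, 0.85): 94%, 90%, 86%
- against the raw contrast (ratios 0.91, 0.75, 0.51): 84%, 90%, 98%

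The 80% starting point is hypothetical, because the protocol claims no power for these endpoints.

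**Chance baseline difference.** Its standard error at 142 per arm is √(2/142) = 0.119 SD. A difference of Δ moves the raw contrast by ρΔ and the change contrast by (ρ − 1)Δ. For Δ = 0.10 SD this is +0.03 to +0.07 SD for the raw contrast and −0.07 to −0.03 SD for the change contrast. The change contrast over-corrects; adjustment removes the shift.

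**Shift caused by knowing the arm.** Suppose disclosure moves the baseline score by δ and leaves follow-up untouched. The raw contrast is then unaffected, the change contrast is off by the whole of δ, and the adjusted contrast by about ρδ.

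The variance figures are for the linear models. For the ordinal NRS model they show direction only.

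**The case against.** The strongest reply is that baseline is already in the analysis. The assessment list and the schedule treat it as one visit among several, so a treatment×time model is naturally read with baseline as a time level. That is plausible, and it means raw imbalance is not simply carried forward. It does not rescue efficiency: the change contrast over-corrects and is the less precise choice at every ρ below 1. The loss is modest when ρ is high, 15% of variance at 0.7.

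A second reply is that this baseline is not a clean pre-randomization covariate, because it is completed after disclosure in an open-label trial. This stands as a real cost against the raw contrast. It is no defence of the change contrast, which takes on the full shift. No questionnaire before disclosure is scheduled, so the problem cannot be avoided by picking another reading.

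A third reply is that such detail belongs in an analysis plan. That would hold if the protocol were silent, but it names covariates for these models in three places and the baseline score is in none.

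A fourth is that the visit structure limits any comparison. This also stands. The two-month postoperative visit exists only in the surgery arm, and the second and third retrievals are reached only by women who go on to further cycles, so 142 per arm does not describe those visits.

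**Conclusion.** The point holds for the EHP-30, EQ-5D and NRS models. As written they are less precise than a baseline-adjusted model on either reading of time. For the linear models the avoidable single-visit variance is 15% to 35% against a change contrast and 9% to 49% against a raw one. This rests on an assumed ρ of 0.3 to 0.7 and equal variances. For NRS only the direction is claimed.

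A reader might infer that the QALY analysis also fails to adjust for baseline EQ-5D, so that chance differences in starting utility pass into the ICER. The documents do not show this. The protocol says "Quality-Adjusted Life Years (QALY) will be computed using data from the EQ-5D instrument" and "Incremental cost-effectiveness ratios (ICER) will be calculated based on QALYs", but states no QALY regression from which a term could be missing. Its remark "Variations in changes to health status and quality of life will be utilized for a cost-utility analysis" points, if anything, towards change rather than raw level. That detail may sit in an analysis plan that is not at hand.

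A reader might also infer that baseline imbalance is carried forward unaltered. That follows only if the models use post-baseline visits alone, which the protocol leaves open.

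The protocol classes the secondary endpoints as supportive and exploratory, so the live-birth conclusion is untouched.

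**What to change.** In the EHP-30, EQ-5D and NRS model descriptions:

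- Use post-baseline scores as responses, and add the baseline value of the same score and a baseline×time term to the covariates.
- Report arm differences only at visits scheduled in both arms, chiefly the first oocyte retrieval, two months after it, and the three-year follow-up. Leave the surgery-only postoperative visit out of the arm comparison, and treat visits at and after the second and third retrievals as descriptive. Give the number contributing per arm at each visit.
- State that baseline is completed after disclosure of the arm, and show the unadjusted follow-up difference beside the adjusted one.
- State how missing baseline questionnaires are handled within the model. The protocol's complete-case rule for models needing complete covariates could otherwise drop these women. Simple baseline imputation or a missing-value indicator relies on baseline being independent of arm, which is doubtful here.

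The cost is a few lines of analysis text and no new data. The price to state openly is that adjustment can carry about ρ times any shift caused by knowing the arm.

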**NRS pain (ordinal: mild 1–3, moderate 4–6, severe 7–10):**
Analyzed using a generalized linear mixed model (GLMM) with cumulative logit link (ordinal logistic regression), including random intercepts for participants, fixed effects for treatment, time, and treatment×time, and prespecified covariates (age, BMI, AMH, center).

**Health economics**
A cost-effectiveness analysis will be conducted from the healthcare perspective. Incremental cost-effectiveness ratios (ICER) will be calculated based on QALYs, and probabilistic sensitivity analyses will be performed to address parameter uncertainty.

**Additional analysis**

– Exploratory subgroup analyses will not be adjusted for multiplicity.

– Safety outcomes will be summarized descriptively by treatment group (frequency, severity, relation to treatment).
– All available data will be used, including outliers.
– Missing outcome data will be handled under the missing-at-random assumption via maximum likelihood in mixed models; for regression models requiring complete covariates, complete-case analysis will be applied.

Covariates

Primary and secondary outcomes will be adjusted for prespecified covariates (age, BMI, AMH, ART type, center), chosen based on clinical relevance and prior evidence.

POWER CALCULATION AND SAMPLE SIZE

The sample size calculation was based on a two-sample comparison of proportions with a two-sided α=0.05 and 80% power. Based on observational data (18, 19), the cumulative live birth rate (CLBR) after three IVF cycles was assumed to be 55% in the ART-only group and 71% in the surgery+ART group (relative risk ≈1.29). This yields a required sample size of 142 participants per arm (284 total). Allowing for 20% attrition, the planned total sample size is 350 participants.

The necessary sample size for this study is estimated to 323 patients to accommodate a statistical analysis method. This estimation uses the 'pwr' package in R, specifically employing the power.prop.test method, which is designed to compare two proportions. This method is more aligned with contemporary statistical practices and provides a clear, transparent methodology for determining the required sample size based on expected success rates.

This means inclusion of 29 patients from/each center/year and 15 surgeries/year. In a Swedish study published in 2022 the prevalence of endometriosis in patients referred for ART-treatment was 21.8% and 17.2% of women had DE (14). In 2021 almost 10 500 IVF cycles were performed in Sweden, while more than 5 500 of those were first-time IVF/ICSI with autologous gametes ((46) Figure 22).

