# STUDY FLOW CHART

# SCHEDULE OF EVENTS TABLE

| Procedures | **Baseline** | **Enrolment** | **1 month prior to surgery or start of first ART cycle^1^** | **Surgery^2^** | **2 months postoperative visit^2^** | **1:st oocyte retrieval** | **2 months after 1:st oocyte retrieval** | **2:nd oocyte retrieval** | **2 months after 2:nd oocyte retrieval** | **3:rd oocyte retrieval** | **2 months after 3:rd oocyte retrieval** | **Visit, phone call or questionnaire 3 years after first treatment (surgery or first ART cykle)** |
| --- | --- | --- | --- | --- | --- | --- | --- | --- | --- | --- | --- | --- |
| **Informed consent oral and written** | x |  |  |  |  |  |  |  |  |  |  |  |
| **Demographics** |  |  | x |  |  |  |  |  |  |  |  |  |
| **Record ultrasound and/or MRI staging according to AAGL and #ENZIAN staging system** | x |  |  |  |  |  |  |  |  |  |  |  |
| **Randomization** |  | x |  |  |  |  |  |  |  |  |  |  |
| **Record surgical procedure according to AAGL and #ENZIAN staging system** |  |  |  | x |  |  |  |  |  |  |  |  |
| **Record intraoperative complications^3^** |  |  |  | x |  |  |  |  |  |  |  |  |
| **Hospital stay** |  |  |  | x |  |  |  |  |  |  |  |  |
| **Record 8 weeks postoperative complications^4^** |  |  |  |  | x |  |  |  |  |  |  |  |
| **EHP-30, EQ5D and NRS scale^5^** |  |  | x |  | x | x | x | x | x | x | x | x |
| **Primary outcome (CLBR)** |  |  |  |  |  |  |  |  |  |  |  | x |
| **Secondary outcome/IVF cycle^6^** |  |  |  |  |  |  | x | x | x | x | x | x |

^1^ start of FSH injections ^2^only first line surgery group ^3^According to Classic ^4^According to Clavien Dindo ^5^Endometriosis Health Profile and Numeric Rating Scale ^6^LBR, PR, number of oocytes retrieved, fertilization grade, number of blastocysts

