# STATISTICAL CONSIDERATIONS

The primary exposure is the randomized allocation (surgery prior to ART vs ART alone). All analyses will follow the intention-to-treat (ITT) principle, meaning participants are analyzed according to their randomized group regardless of adherence. Per-protocol and as-treated analyses will be conducted as sensitivity analyses to assess robustness. An interim analysis at the halfway point is planned to monitor potential adverse effects and ensure the safety of the interventions.

No formal adjustment for multiplicity will be made; the primary endpoint will be tested at a two-sided α=0.05, while secondary endpoints are considered supportive and exploratory. Sensitivity analyses will address protocol deviations, handling of missing data, and robustness to alternative modelling approaches.

DATA ANALYSES

Baseline demographic and patient’s characteristics will be summarized by treatment group. Continuous variables will be described with mean, standard deviation, median, interquartile range, minimum and maximum, and categorical variables with counts and percentages.

Primary endpoint

The primary endpoint of the study is the Cumulative Live Birth Rate (CLBR), defined as the proportion of participants achieving at least one live birth within three years following the initiation of treatment.

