# DATA MANAGEMENT AND QUALITY CONTROL

DATA COLLECTION

Data for the randomized controlled study will be collected from medical records. In case of missing information patients will be contacted by phone or through secure electronic data platforms (e.g “Alltid Öppet”) for additional information. Data from ultrasound examination, surgeries and IVF treatments will be documented either directly into the eCRF or in paper forms. The results from the blood samples (AMH and P-Progesteron) will be collected from the medical records. No blood samples will be stored for future use in this study.

For the sub-studies data will be collected from the following sources:

- Quality of Life: Questionnaires are sent from the eCRF RedCap and patients´ answers will be electronically collected directly into the eCRF.
- Health Economy: Cost per patient will be collected from each site’s economical system.
- Adenomyosis: Medical records and Data forms or paper forms as described above.
- P-Progesterone: Medical records and Data forms or paper forms as described above.
- Obstetrical Outcomes: Either from medical records or the MFR at the end of the study. If data is missing, patients can be contacted by phone or through secure electronic data platforms (e.g “Alltid Öppet”) for additional information.
- Prospective cohort study: Data will be collected in the same way as in the RCT.
- Long-term follow up: Data will be collected from Q-IVF, MFR, Gynop and the Swedish National Pregnancy Register. We will use the unique Swedish identification number to identify the patients from the registers.
- P-Progesterone and reproductive outcome: Data will be collected in the same way as in the RCT.

SOURCE DATA AND CASE REPORT FORM

Patient medical records will serve as the source data and will be stored in accordance with Good Clinical Practice (GCP) guidelines. Data for this study will be captured using the Research Electronic Data Capture (RedCap) system, utilizing an electronic Case Report Form (eCRF). The information will be transcribed from paper source documents onto the eCRF by the site. To ensure accurate and reliable data collection, the study monitor will conduct verification and cross-check of the eCRFs against the investigator’s records (source document verification). The study database is located in Sweden at Clinical Trials Office (CTO), Center for Clinical Cancer Studies, Karolinska University Hospital.

DATA RECORDING AND RECORD KEEPING

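### The complete-case rule would drop women with a known outcome but no AMH value from the adjusted analyses

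*Protocol*

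**What the plan says.** The Additional analysis list sets two rules for missing data. Missing outcomes are handled by maximum likelihood in the mixed models, assuming missingness at random. For covariates, "for regression models requiring complete covariates, complete-case analysis will be applied". The bullet just before commits the analysis to all the data at hand, outliers included.

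AMH enters the adjusted models in these places:

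- The Primary analysis section reports a crude relative risk, then an adjusted one with age, BMI, AMH, ART type and center.
- The Time-to-Event section estimates effects on live birth and pregnancy by Cox models adjusted for the prespecified covariates. It names no unadjusted hazard ratio.
- The EHP-30, EQ-5D and NRS models adjust for age, BMI, AMH and center.
- The Covariates paragraph extends adjustment to primary and secondary outcomes generally.

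On how AMH is obtained, Data Management says: "The results from the blood samples (AMH and P-Progesteron) will be collected from the medical records".

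**The concern.** In a trial of this size a covariate is added to gain precision. A rule that deletes a woman because that covariate is missing gives some of the precision back and discards an outcome that is already known.

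AMH is the covariate most exposed. It is not among the eligibility criteria, the schedule of events has no row for it, and ART is given under each unit's own routine, possibly at regional units.

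Three consequences follow:

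- Crude and adjusted relative risks may differ partly because they rest on different women, so the comparison between them is hard to read.
- For time to live birth and time to pregnancy, the adjusted Cox model is the only effect estimate named, so no unadjusted hazard ratio is planned to fall back on.
- In the mixed models, one missing AMH value removes all of a woman's questionnaires. The schedule allows up to nine in the surgery arm and eight in the ART arm. The maximum-likelihood handling promised for missing outcomes cannot help her.

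**Working it through.** **1. Which covariates can be missing.** Age and BMI are inclusion criteria, verified before assignment, and center is the randomisation stratum, so all three should be nearly complete. AMH has no such safeguard. ART type is a different kind of problem and is left out of the figures below.

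**2. Reproducing the plan's sample size.** The inputs, from Power Calculation and Sample Size, are a "two-sample comparison of proportions with a two-sided α=0.05 and 80% power" and live-birth rates of 55% and 71%. The mean rate is 0.63 and the difference 0.16.

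n per arm = [1.960 × √(2 × 0.63 × 0.37) + 0.842 × √(0.55 × 0.45 + 0.71 × 0.29)]² / 0.16²
= [1.960 × 0.6828 + 0.842 × 0.6734]² / 0.0256 = 141.8, so 142 per arm and 284 in total.

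This matches the plan. For attrition the plan says: "Allowing for 20% attrition, the planned total sample size is 350 participants". 284 / 0.80 = 355, so 350 is close. It means 175 per arm randomised and 175 × 0.80 = 140 per arm after attrition.

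**3. Effect of deletion.** The protocol gives no rate of missing AMH, so the share m is an assumption. It is taken as equal in both arms and unrelated to outcome.

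Women dropped = 350 × m. Power at n per arm = Φ[(0.16√n − 1.960 × 0.6828) / 0.6734].

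| Assumed share without AMH | Dropped of 350 | n per arm from 140 | Power | n per arm from 175 | Power |
|---|---|---|---|---|---|
| 0% | 0 | 140 | 79.5% | 175 | 87.6% |
| 2% | 7 | 137.2 | 78.7% | 171.5 | 87.0% |
| 5% | 17.5 (about 18) | 133 | 77.4% | 166.25 | 85.9% |
| 10% | 35 | 126 | 75.2% | 157.5 | 84.0% |

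If all 350 outcomes were known, the live births discarded would be m × 175 × (0.55 + 0.71), or about 4, 11 and 22. If attrition leaves 280 known outcomes, the women dropped among them number 280 × m, or about 6, 14 and 28.

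At 5% missing, the confidence interval widens by a factor of about 1/√0.95 = 1.026.

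These power figures come from the unadjusted two-proportion test. They serve as a yardstick for lost information, not as the power of any adjusted model.

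**The case against.** The strongest reply is that the main comparison is safe. The first-named primary analysis is the crude relative risk, which needs no covariates and loses no woman with a known outcome. The sample size rests on that comparison and not on the adjusted models. This stands, and it limits the point to the adjusted analyses.

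A reader might infer that the rule breaks the protocol's statement that "All analyses will follow the intention-to-treat (ITT) principle". The text does not support this. The protocol goes on to define the principle as analysis by randomised group whatever the adherence. Complete-case deletion moves nobody between arms and does not depend on adherence. The conflict is with the commitment to use all available data. Even that line could be read as mainly about outliers, though its wording is not so limited.

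A reader might also infer that BMI will often be missing, because the schedule marks demographics in the column headed "1 month prior to surgery or start of first ART cycle", after randomisation. This does not hold either. BMI must be known to establish eligibility. Women withdrawn between randomisation and treatment are to be replaced, and the outcome period starts only at first treatment. Such women are not known outcomes lost through a missing covariate.

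Two mitigations have some force. The protocol promises sensitivity analyses on missing data and contact with patients to retrieve missing information. Ovarian reserve is also considered when stimulation is chosen, so most women may have an AMH value. But the sensitivity analyses are unspecified and leave deletion as the main rule. A patient cannot supply a laboratory value that was never measured. Ovarian reserve can also be judged from the antral follicle count, which the protocol lists separately.

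**Conclusion.** The point holds for the adjusted analyses and for AMH. The protocol itself fixes the deletion rule, so this is not a matter left open for an analysis plan.

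The loss is modest: about 2 power points at 5% missing (79.5% to 77.4% from 140 per arm) and about 4 at 10% (79.5% to 75.2%). Both rest on assumed shares with missingness unrelated to arm and outcome. The documents neither give a rate nor show that AMH will often be missing.

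The crude primary relative risk is not threatened, and no breach of the stated intention-to-treat definition is shown. The case for change is that the rule discards known outcomes for no benefit and blurs the crude-versus-adjusted comparison, while a better rule costs almost nothing.

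ART type lies outside this verdict. It is recorded during treatment and does not exist for a woman who conceives without ART. Filling in values cannot repair that, so its place in the adjustment set needs separate correction.

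**What to change.** Replace the complete-case clause in Additional analysis with wording such as:

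> Missing baseline covariates will be filled in, blind to arm and outcome: by the overall mean plus a missing indicator if AMH is used as a continuous variable, or by a separate missing category if AMH is categorised. No randomised woman with an outcome is excluded from an adjusted analysis for a missing baseline covariate. Complete-case analysis and multiple imputation are sensitivity analyses.

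Both forms are needed because the protocol defines AMH in three categories for subgroups and baseline description but does not say which form enters the models. In a randomised comparison, filling in a pre-treatment covariate in this way does not bias the arm contrast. The promise must stay limited to baseline covariates, because it cannot be kept for ART type.

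The cost is one sentence and a little more programming, with no new data.
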